##### Youth participatory action research (YPAR)

To measure the participatory experience of youth researchers, we will employ a mixed-methods approach guided by the 7Ps Framework by Cahill and Dadvand (2018) [34]. This framework examines youth participation through seven interrelated dimensions: purpose, positioning, power relations, perspectives, protection, place, and process. Quantitative data will be collected using a structured survey with a 5-point Likert scale. We will collect qualitative data through weekly reflective diaries, monthly meetings, and exit in-depth interviews. The reflective diaries will be completed by the youth researchers with entries of planned activities for the week, achievements, personal reflections, challenges encountered, strategies used to address those challenges, and any support required.

##### Other measures

Other study parameters include pre-specified sociodemographic characteristics e, which will serve as equity indicators (i.e., gender, age, education level, family economic status, and residence) (see Table 1). These were chosen based on prior literature [62] and will be used for exploratory subgroup analyses to assess whether the effect of the intervention differs across subgroups [63].

### Procedures

#### Translation and cultural adaptation

Before the recruitment of participants, a WHO-guided adaptation process [64] was followed to translate and culturally adapt study materials to the Kenyan context. This included English versions of EMA items and digital intervention element content. The adaptation process included forward and backward translation with help from local experts and youth researchers, consensus team meetings, piloting tools for item clarity, and a final consensus meeting (Supplementary methods 4 and Table 2).

#### Screening and recruitment

The research team will contact schools, universities, and youth organizations to seek permission to engage with young people. Following initial visits and an official letter detailing the nature of the research, we will collaborate with the institution heads to organize the initial information sessions with young people. Interested young people will receive detailed study information by the research team, and before signing consent or assent (i.e., for minors) forms. Minors (i.e., below 18 years) will also get information sheets and consent forms for their guardians. Participation is voluntary, and young people can withdraw at any time. Data collected up to the point of withdrawal will be retained for analysis once anonymized.

After enrollment, screening will be used to identify who meets the inclusion criteria. Participants will fill in self-reported psychometric and sociodemographic measures (see above), and take a short Social and Occupational Functioning Assessment Scale (SOFAS) interview conducted by trained research staff [65].

#### Randomization and blinding

After screening and baseline data collection, participants will be randomized at the cluster level to one of the four study arms using permuted block randomization with blocks of four clusters each. To minimize the risk of cross-contamination within schools and small community-based organizations, naturally occurring sub-groups (e.g., class levels in schools) will be treated as allocation units and assigned to the same intervention arm. In case of community-based organizations, which are community-led groups based on shared interests (e.g., sports initiatives) [66], participants from a given CBO will be randomized to the same intervention condition. The randomization procedure will be carried out centrally and off-site using a computer-generated allocation sequence. Participant personal identification data will be stored separately from the process and outcome data. Assessors will be blind to the allocation of participants, data specific to the experimental groups will be stored separately and breaks in masking will be documented. Unblinding of assessors will only occur in exceptional cases where knowledge of the allocation is necessary for participant safety.

#### Data collection

Measures will be assessed at two time points: baseline (i.e., before randomization, also used for screening) and post-intervention (i.e., after the 28-day intervention period). To assess primary and secondary outcomes, participants will complete self-report measures using *Redcap* [67], a secure electronic data capture system with built-in quality control features (e.g., logic checks), and participate in interviews and FGDs (see Table 1 - Additional File 2). All data collection tools will be administered in English.

During the intervention phase, participants assigned to the digital or blended intervention arms will receive four mood checks daily with two alternating EMA item sets each day, scheduled at random within set blocks of time. For proximal effects assessment, participants will be prompted to reply to a post-EMI EMA with three items after each momentary intervention component. Morning and evening EMA will be collected at participant-defined times. A research team member will routinely review incoming data for completeness and consistency. Additional data cleaning steps will be performed before analysis to ensure data integrity.

Qualitative data collection will follow the principle of information power, i.e., stopping at the point at which no new information is obtained and redundancy is reached [68]. If possible, interviews will be conducted face-to-face.

Data collection will be conducted by a research team consisting of a PI, co-investigators, doctoral students, youth researchers, and local researchers. The data collection team will be fluent in English with experience in using both quantitative and qualitative methodologies.

The feasibility of all tools, including EMA, was piloted in the co-design phase with adolescents and young people who tested the questionnaires, EMA, and EMI over 2 weeks. Their feedback indicated that the number and frequency of items were manageable. Based on this pilot, several adaptations were implemented to further reduce participant burden, such as allowing users to adjust prompt times and enabling a ‘do-not-disturb’ mode.

### Data processing and analysis

#### Quantitative data

A detailed statistical analysis plan will be published before conducting any analyses. Data will be accessed only after completion of the final post-intervention data collection. Data will be analyzed according to the intention-to-treat principle. Data processing will involve cleaning, (re-) coding, and formatting of variables for statistical analysis. The sample size was calculated using the Shiny CRT Calculator [69]. Using a parallel design with baseline measure and assuming an average intra-cluster correlation (ICC) of 0.05 [70], and α = 0.05, 25 clusters per arm with 6 participants each (600 participants) will yield 80% power (β = 0.8) to detect a mean difference of ≥ 0.36 between the blended intervention and the control condition (CAU). The assumed minimal mean difference aligns with effects observed in previous RCTs evaluating the individual intervention elements [27, 30]. Considering a 10% dropout rate, 666 young people will need to be recruited.

The primary analysis will apply a mixed-effects linear regression model to examine the effect of the blended intervention compared to the control condition (CAU) on emotion regulation difficulties. The level of ER difficulties will be compared between the experimental and the control conditions at post-intervention. ER difficulties (DERS-SF) at post-intervention will be entered as the dependent variable, and ER difficulties at baseline, condition (= allocation), and setting (= location or context in which participants receive the intervention) will be entered as independent variables. While random allocation to intervention arms is designed to balance baseline characteristics, we will verify balance post-randomization and – if imbalance is identified – incorporate appropriate covariate adjustments to improve precision and validity of effect estimates. To account for clustering, the model will include a random intercept for the allocation unit (i.e., face-to-face group), with individual (level 1) nested within these units (level 2), reflecting the two-level structure. The model will be fitted using Restricted Maximum Likelihood (REML), and the main effect of condition will be estimated using a Wald-type test (α = 0.05). Potential regression to the mean will be considered in the interpretation of results.

Secondary measures - including positive and negative affect, symptoms of depression, anxiety, and stress, emotional reactivity, emotion beliefs, ER strategies, and interpersonal ER - will be analyzed using mixed-effects linear regression models, consistent with the approach described for the primary analysis. Exploratory analyses comparing the other intervention conditions (e.g., face-to-face and digital only against CAU) will be conducted to explore the potential contribution of intervention elements to overall effects and generate hypotheses for future implementation.

Exploratory analyses will include subgroup analysis to examine whether signals of efficacy of the blended intervention differ across specific groups. These analyses will be conducted within the primary mixed-effects model using interaction terms. We will examine proximal signals of efficacy of digital intervention components using data from the micro-randomized trial. Mixed-effects linear regression models with EMA observations (level 1) nested within individuals (level 2) will be applied to account for the hierarchical structure of longitudinal EMA data. Variables will include momentary negative affect, stress, and momentary ER. EMA data before and after momentary intervention components will be compared and types of EMI exercises (i.e., breathing, imagery, diary, control) will be included as independent variables. Results from all exploratory analyses will be interpreted using effect sizes and 95% confidence intervals rather than formal significance testing. Data from the process evaluation, acceptability, desirability, usability, and safety, sample characteristics, and baseline measures will be summarized descriptively.

We assume data will be Missing at Random (MAR) and will explore missingness patterns to assess this assumption. Continuous variables will be presented using means and standard deviations or medians and interquartile ranges; categorical variables using frequencies and percentages. All statistical analyses will be conducted in R.

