### Participants

The study will recruit 666 young people aged 13–25 from Nairobi and the surrounding towns, Kenya, who exhibit difficulties in ER as assessed with the Difficulties in Emotion Regulation Scale (DERS) [38], i.e., an indicated population. Participants will be eligible if they score above pre-defined thresholds on the DERS-SF subscale, specifically: DERS Strategies = 3, Non-Acceptance = 3, Impulse = 2.5, Goals = 3.5, Awareness = 3.5, and Clarity = 3 [38, 39]. Young people experiencing acute suicidal thoughts or low functionality will be excluded but offered up to 2 counselling sessions (see Supplementary Table 1).

For a heterogeneous and generalizable sample, we will recruit young people from different socio-economic backgrounds, sexes, and educational levels. Recruitment will take place across at least four high schools, one university, and five community-based organizations (CBOs) or programs for out-of-school individuals in Nairobi to capture a broad range of social contexts. Recruitment logs will be closely monitored to ensure balance across these characteristics.

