### Outcome measures

#### Primary outcomes

The primary outcome will be ER difficulties at post-intervention, while controlling for baseline differences, assessed with the DERS-SF [38] (see Table 1). The DERS-SF is a validated self-report measure with 18 questions organized in six subscales and rated on a 5-point Likert scale. DERS-SF demonstrates good internal consistency (α = 0.89) [38] and acceptable test-retest reliability (*r* = 0.67) [45]. The total sum score across all subscales will be compared between the blended intervention and the control condition.

**Table 1 Tab1:** An overview of measures and time points

Time points				
**Construct**	**Measures/Tools**	**Screening and Baseline (T0)**	**Throughout the intervention phase (T1)**	**Post-intervention (T2)**
*Screening measures*				
Sociodemographic characteristics	Demographic health survey questions on gender, age, education level, family economic status, and residence	X		
Functioning	Social and Occupational Functioning Assessment Scale (SOFAS) (63)	X		
Suicidality, Substance Use, Wellbeing	Community Quick Screening Tool (CQST) (66)	X		
*Primary outcome (Non-momentary)*				
Difficulties in Emotion Regulation	Difficulties in Emotion Regulation Scale (DERS-SF) (43)	X		X
*Secondary outcomes (Non-momentary)*				
Depression, anxiety, and stress	Depression Anxiety Stress Scale (DASS-21) (46)	X		X
Emotion Regulation	Emotion Beliefs Questionnaire (EBQ)(48)	X		X
	Emotion Regulation Questionnaire (ERQ)(49)	X		X
	Interpersonal Emotion Regulation Questionnaire (IERQ)(50)	X		X
Emotional reactivity	Short form of the Perth Emotional Reactivity Scale (PERS-S)(47)	X		X
Positive and negative affect	Positive And Negative Affect Schedule (PANAS)(45)	X		X
*Secondary outcomes (momentary)*				
Difficulties in Emotion Regulation	Eight alternating items of the State Difficulties in Emotion Regulation Scale (S-DERS)(56)		X	
Affect valence and arousal	Four bipolar VAS and one multiple-choice EMA item		X	
Event-related stress	Two VAS items assessing occurrence and intensity		X	
Emotion regulation capacity	Two alternating VAS items		X	
Social context	Two multiple-choice items		X	
Activities	One multiple-choice item		X	
Perceived Emotion regulation success (only Post-EMI EMA)	One VAS item		X	
Sleep quality (only morning check-in)	One VAS item		X	
Expectation about the day (only morning check-in)	One VAS item		X	
Reflection on the day (only evening check-in)	One VAS item		X	

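### The power calculation and the primary model take the face-to-face group of about 6 as the cluster, but the randomisation section allocates class levels and whole community organisations, so the stated 80% power does not follow from the design described

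*Protocol article*

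**What the plan says.** All references are to the protocol article.

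- **Quantitative data** (sample size): "25 clusters per arm with 6 participants each (600 participants) will yield 80% power", "assuming an average intra-cluster correlation (ICC) of 0.05", for a difference of at least "0.36 between the blended intervention and the control condition (CAU"). The design option is given as "Using a parallel design with baseline measure". No baseline correlation is stated. The same section puts the primary model's random intercept at the allocation unit and identifies that unit as the face-to-face group.
- **Face-to-face intervention element**: groups hold 6 to 7 young people.
- **Randomization and blinding**: the allocation units are naturally occurring sub-groups, with class levels as the example for schools. For CBOs, "participants from a given CBO will be randomized to the same intervention condition".
- **Strengths and limitations**: clustering by class level is named again as the protection against contamination.
- **Participants**: "Recruitment will take place across at least four high schools, one university, and five community-based organizations (CBOs") or similar programmes.
- **Primary outcomes**: "The total sum score across all subscales will be compared between the blended intervention and the control condition".

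**The concern.** Two different clusters are in use. The calculation and the model work with the face-to-face group. The randomisation works with a class level or a whole CBO, which may contain several such groups. In a cluster trial, precision depends mainly on the number of units randomised. If several groups of 6 share one randomised unit, there are fewer and larger clusters than the calculation assumes, and a null result would be read as coming from a trial with 80% power when that was not shown.

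The face-to-face group also cannot be the unit throughout. The digital-only and care-as-usual arms receive no group sessions, and care as usual is one side of the primary comparison.

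The model is affected in the same way. With a random intercept at the group, two groups from the same class level count as independent. Any variance between class levels or CBOs is then spread over too many units, and the standard error of the treatment effect is too small.

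**Working it through.** **1. Reproduce the stated figure.** Inputs from Quantitative data: k = 25 clusters per arm, m = 6, ICC = 0.05, two-sided α = 0.05 (the article does not state sidedness). Assumption: 0.36 is in SD units, since no SD is given.

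- Design effect: 1 + (m − 1) × ICC = 1 + 5 × 0.05 = 1.25.
- Effective size per arm: 150 / 1.25 = 120.
- SE = √(2 × 1.25 / 150) = 0.129 SD.
- Detectable difference at 80%: (1.96 + 0.8416) × 0.129 = 0.362 SD.
- Power at 0.36: 79.6% (normal) or 78.0% (t, 48 df).

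Allowing a baseline period with cluster autocorrelation 0.8 and individual autocorrelation 0 gives 81.1% (normal) or 79.5% (t). The arithmetic is sound for 4 × 25 = 100 randomised clusters of 6.

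**2. Compare with the sites listed.** One unit per CBO gives 5. The remaining 100 − 5 = 95 must come from 4 schools + 1 university = 5 institutions, which is 95 / 5 = 19 units each, with about 6 evaluable participants per unit. Class levels would not plausibly reach that number.

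**3. Illustrate the effect of fewer units.** The number of units is not stated, so the counts below are assumptions. Held fixed: 150 evaluable per arm, ICC 0.05, 0.36 SD, equal unit sizes, no gain from baseline. For K units in total, k = K/4, m = 600/K, SE = √(2 × [1 + (m − 1) × 0.05] / 150), df = 2k − 2, and power comes from the noncentral t with noncentrality 0.36/SE.

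| Units in total | Evaluable per unit | Design effect | Power (t) | Detectable difference (SD) |
|---|---|---|---|---|
| 100 | 6 | 1.25 | 78% | 0.37 |
| 80 | 7.5 | 1.325 | 75% | 0.38 |
| 60 | 10 | 1.45 | 71% | 0.40 |
| 40 | 15 | 1.70 | 62% | 0.45 |
| 25 | 24 | 2.15 | 49% | 0.52 |

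**4. Sensitivity to baseline adjustment.** Multiply the variance by 1 − r², where r is the baseline to follow-up correlation of the cluster means. The document's test-retest figure for the DERS-SF, 0.67, is borrowed as an assumption.

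| Assumption | Power, 25 units | Power, 40 units |
|---|---|---|
| 0.67 at individual level, 0 at cluster level | 52% | 68% |
| 0.67 at both levels | 74% | 86% |
| 0.67 at individual level, 0.8 at cluster level | 82% | 91% |

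The last assumption would give about 97% for 25 clusters of 6 per arm, so the stated 80% did not rely on it.

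**5. The model.** For illustration, suppose all between-cluster variance lies at the randomised unit, with ICC 0.05. A group-level intercept then works with a design effect near 1.25, while the true one is 1.70 for units of 15 or 2.15 for units of 24. The standard error would be understated by a factor of about √(1.25/1.70) = 0.86 or √(1.25/2.15) = 0.76.

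**The case against.** The strongest reply is that the documents do not prove a shortfall. Sites are given as a minimum, class level is only an example of a sub-group, university units are not described, and the analysis section itself names the face-to-face group as the allocation unit. A planned analysis with baseline adjustment may also recover much of any loss, and the ICC for larger natural units may be below 0.05: at an assumed 0.02 with no baseline gain, power is 65% for 25 units and 74% for 40. An article may also leave a count of units by setting to the full protocol or the analysis plan.

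Most of this stands, and it rules out two stronger readings.

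- A reader might infer that the design yields roughly 25 to 40 clusters. That needs invented inputs: four class levels per school and four university sub-groups give 16 + 5 + 4 = 25, while six levels and eleven sub-groups give 24 + 5 + 11 = 40. The documents give neither set.
- A reader might infer that the trial does not have 80% power. Step 4 shows that it could exceed 80% even with 25 or 40 units, depending on correlations that the article does not state.

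The mismatch itself is untouched. The article fixes the power, the cluster size and the allocation unit, and these disagree. Calling the unit a face-to-face group cannot settle it, because two of the four arms have no such groups and each CBO goes to one arm as a whole.

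**Conclusion.** The point holds as an inconsistency of unit. The stated 80% and 0.36 are calculated correctly for 100 randomised clusters of 6, but those clusters are not the units that the randomisation section allocates, and the listed minimum of sites would not plausibly supply 100 of them. The claimed power therefore does not follow from the design described.

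The size of the loss is not known. On the stated ICC, equal unit sizes, 150 evaluable per arm and no baseline gain, power would lie between 75% (80 units) and 49% (25 units). A strong baseline correlation at both levels could offset much of this. The misplaced random intercept is a separate consequence: it affects the validity of the primary test whenever several groups share one randomised unit.

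Two slips in the same passage are minor. β is printed as 0.8 where 80% power means 0.2. And 0.36 is called a mean difference without a unit, although the outcome is a sum of 18 items on a 5-point scale. It reproduces only as a standardised difference, so a literal reading in scale points is not what was calculated.

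**What to change.** 1. Reconcile the Participants, Randomization and blinding, and Quantitative data sections on one definition of the allocation unit that applies in all four arms, and state how many units each setting supplies.
2. Restate power and detectable difference for that unit, using the actual number and size distribution of units, the ICC, an explicit baseline correlation at individual and at cluster level, and small-sample degrees of freedom.
3. Place the random intercept of the primary model at the randomised unit.
4. Minor edits: write β = 0.2, and label 0.36 as a standardised difference with its equivalent in DERS-SF points.

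The cost is a revised sample-size paragraph and one changed line in the model specification, and the stated figure may become less favourable. No extra participants are needed. Splitting class levels into smaller units would raise the count, but it trades against the protection from contamination that the article chose, and this point does not ask for it.

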## Study methods

### Study design and setting

This protocol was developed following the SPIRIT 2025 Statement [35] (see Additional File 1: Supplementary methods 5) and will be reported in line with CONSORT 2025 guidelines [36]. In a 2 × 2 parallel group, cluster-randomized controlled factorial trial design, young people aged 13–25 with difficulties in ER will be randomly assigned at a ratio of 1:1:1:1 to one of four conditions: (A) the full blended MAISHA intervention, combining the digital with the face-to-face element; (B) the digital app only; (C) the face-to-face element only; or (D) broadly defined care as usual (CAU). Participants will be recruited from high schools, universities, and community-based organizations for out-of-school individuals. Randomization will be conducted off-site using a computer-generated sequence, and outcome assessment and statistical analyses will be blinded. The primary comparison will assess the superiority of the full blended intervention (A) over CAU (D) in reducing ER difficulties. Exploratory comparisons between all intervention conditions will also be conducted to inform future implementation.

Nested within the cluster RCT, we will conduct a micro-randomized trial [37] to determine the proximal effects of digital intervention components and what factors might influence those effects. Using repeated, within-participant randomization to all digital components of the MAISHA intervention, each participant in study arm A (digital and face-to-face elements) and B (digital only) will be randomized to digital intervention components (i.e., breathing, imagery, diary techniques, or control) at multiple time points (decision points) throughout the study. Decision points will be triggered in moments of high negative affect or stress, indicated by a participant’s EMA response crossing a pre-defined threshold (see Fig. 1).

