#### Control condition (Care as Usual)

CAU is broadly defined and includes standard health care services available within the public health system. This includes promotion, prevention, treatment, and rehabilitation of Mental, Neurological, and Substance Use (MNS) disorders for adolescents [40]. CAU is not actively monitored. All interventions will be given in addition to CAU. The control condition will also be put on a waiting list to receive an adjusted version of the digital element after the trial is finished.

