#### Face-to-face intervention element

Building on the Kenyan Shamiri intervention [11], the face-to-face element of maisha involves four group sessions grounded in the wise interventions framework [44]: growth mindset (sessions 1 and 2), gratitude (session 3), and value affirmation (session 4). The sessions will run weekly for 1 h over four weeks, delivered in small groups of 6 to 7 young people by lay providers (aged 18 to 22). Supervision (ratio of 1:5) will be provided by trained clinical psychologists (see Supplementary methods 2).

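### The primary model defines the randomised unit as the face-to-face group, which conflicts with the randomisation section and does not exist in the care-as-usual arm

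*Protocol article*

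**What the plan says.** Under Randomization and blinding, the article describes what is randomised. In schools, "naturally occurring sub-groups (e.g., class levels in schools) will be treated as allocation units and assigned to the same intervention arm". For CBOs, "participants from a given CBO will be randomized to the same intervention condition".

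Under Quantitative data, it describes the primary model: "the model will include a random intercept for the allocation unit (i.e., face-to-face group"). Participants are level 1 and these groups level 2, and no further level is named. The secondary outcomes use the same approach.

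Under Face-to-face intervention element, the groups appear as a mode of delivery, "delivered in small groups of 6 to 7 young people by lay providers". Only arms A (blended) and C (face-to-face only) receive that element.

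Under Study design and setting, "The primary comparison will assess the superiority of the full blended intervention (A) over CAU (D) in reducing ER difficulties". Under Control condition, "CAU is broadly defined and includes standard health care services available within the public health system". No group sessions are described for CAU.

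The sample size paragraph assumes 25 clusters of 6 per arm, an ICC of 0.05 and alpha of 0.05. The Participants section names a minimum of four high schools, one university and five CBOs or programmes.

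**The concern.** A cluster trial has to carry the randomised unit in its analysis, because the people in that unit share both an allocation and a context. The article names the right thing, the allocation unit, and then defines it as something else. Two problems follow if an analyst takes the definition at its word.

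First, half of the primary comparison has no such unit. The analyst would have to invent groups for CAU participants, enter each as a cluster of one, or disregard the definition. These choices give different standard errors.

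Second, a class level or CBO with more than about seven participants in arm A would be split into several groups, which the model would treat as independent. Variation between randomised units would then be averaged over too many apparent clusters. The confidence interval for the confirmatory comparison would be too narrow, and a false claim of superiority would be more likely than the nominal 5%. The secondary models would inherit the same fault.

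**Working it through.** **Inputs.** From the Quantitative data section: 25 clusters per arm of 6, hence 150 analysed per arm; ICC 0.05; alpha 0.05 (taken as two-sided); difference 0.36 (taken in SD units, as no SD is stated); 80% power. The size M of a randomised unit is not stated, so it is varied from 6 to 30.

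**1. The plan's own figure.** Design effect = 1 + (6 − 1) × 0.05 = 1.25. Standard error = √(2 × 1.25/150) = 0.129. Power = Φ(0.36/0.129 − 1.96) = 79.6%, which reproduces the stated 80%. The sample size therefore rests on a randomised unit of about 6.

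**2. Can units be that small?** Four arms of 25 make 100 clusters. At the named minimum of sites, with each CBO as one unit, 100 − 5 = 95 sub-groups must come from four schools and one university, or 95/5 = 19 per institution. The site numbers are minimums, so this does not prove that units are larger, but it makes larger units plausible.

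**3. Type I error if the intercept is on groups of 6.** The true variance of the difference is proportional to D = 1 + (M − 1) × 0.05. The model's variance is proportional to 1.25 when both arms are labelled in groups of 6. If CAU participants are singletons, it is proportional to (1.25 + 1.00)/2 = 1.125. Then:

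type I error = 2 × [1 − Φ(1.96 × √(model/D))]

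For M = 24: D = 2.15; √(1.25/2.15) = 0.762; 1.96 × 0.762 = 1.494; type I error 13.5%.

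| M | D | Model SE / true SE (groups of 6 in both arms) | Type I error, groups of 6 in both arms | Type I error, CAU singletons |
|---|---|---|---|---|
| 6 | 1.25 | 1.00 | 5.0% | 6.3% |
| 12 | 1.55 | 0.90 | 7.8% | 9.5% |
| 24 | 2.15 | 0.76 | 13.5% | 15.6% |
| 30 | 2.45 | 0.71 | 16.2% | 18.4% |

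**4. Simulation check.** REML fits, no true effect, no covariates, 2,000 runs per scenario, critical value 1.96. Whole units only, so 144 per arm for M = 12 and 24.

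| M | Groups of 6 in both arms | CAU singletons | Randomised unit |
|---|---|---|---|
| 6 | 5.9% | 6.4% | 5.4% |
| 12 | 8.2% | 11.2% | 5.8% |
| 24 | 15.0% | 16.4% | 8.4% |
| 30 | 15.7% | 18.0% | 8.6% |

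At M = 6 the first and third models are identical, so 5.9% against 5.4% is simulation noise. The excess that remains in the last column at M = 24 and 30 comes from using 1.96 with only five or six units per arm. It does not come from the choice of unit.

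**5. Power with the randomised unit in the model.** Using D in place of 1.25 in step 1 gives 79.6% for M = 6, 70.7% for M = 12, 56.6% for M = 24 and 51.3% for M = 30.

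**The case against.** The strongest defence is that the article does place the intercept on the allocation unit, and the randomisation section uses the same term for what is randomised. On that reading the model does contain the randomised unit, and only the parenthesis is loose. The planned numbers also fit one group per unit: 666 recruits in 100 clusters is 6.66 each, which matches the stated group size of 6 to 7. In that design, with CAU participants labelled by their own allocation unit, there is no inflation at all.

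This stands in part. It shows that the text equates two units and does not openly replace one with the other. It also shows that inflation depends on a unit size the article does not state. It does not remove the conflict. Nothing says that a class level or CBO holds exactly one group, and the definition cannot apply to CAU whatever the unit size.

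Two further limits are fair. No text says that CAU participants would be entered singly; that is one way of coping with the definition, and at the planned unit size it gives only 6.3%. The calculations also omit the baseline score and the fixed effect for setting. Setting could absorb some variance between sites, but not variance between class levels within a school, and the effect of a single CBO cannot be separated from its arm.

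A reader might also infer an error from the sentence that "the main effect of condition will be estimated using a Wald-type test", since no small-sample degrees of freedom are given. The article does not support that. The wording does not exclude a t or F reference distribution, and a separate detailed analysis plan is promised, which is the usual place for this choice.

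**Conclusion.** The definition of the level-2 unit is wrong as written. It conflicts with the randomisation section and leaves one arm of the primary comparison without a valid cluster identifier. That conclusion rests on the text alone.

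The numerical consequence is conditional. With an ICC of 0.05 and 150 per arm, type I error ranges from 5.0% (units of 6, both arms labelled) to 16.2% (units of 30), or from 6.3% to 18.4% if CAU participants are singletons. Units of 12, 24 and 30 are assumptions, made plausible by 100 clusters against a minimum of ten sites.

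A reader might infer that the primary test is certainly anticonservative, or that the model has no term for the randomised unit under any reading. The article supports neither. Both follow only if the parenthesis is applied literally and units hold several groups or CAU participants are not labelled by unit.

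**What to change.** - Delete the parenthesis that defines the allocation unit as the face-to-face group.
- State that the random intercept is for the unit actually randomised (class level, CBO or university sub-group) in every arm, for the primary and the secondary models.
- State the number and size of the randomised units. If any unit in arms A or C contains several face-to-face groups, add group as a random effect nested in the unit for those arms only. If unit and group coincide, the extra term is redundant.
- Secondary, for the analysis plan: name a small-sample degrees-of-freedom method such as Kenward-Roger or Satterthwaite. This matters mainly if there turn out to be few units per arm.

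The cost is a change of wording and one identifier that randomisation has to generate anyway. If units are single groups of 6, nothing changes and power stays at 79.6%. If units are larger, standard errors grow by √(D/1.25): about 11% for units of 12 (√1.24 = 1.11) and 31% for units of 24 (√1.72 = 1.31). The lower power in step 5 of the working then becomes visible. That loss comes from the size of the units; the corrected model only reveals it.
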